#### Control group

In every cluster designated as a control group, patients aged 65 or older will be selected according to the criteria outlined above. The difference here is that patients will be given only the standard opportunistic screening. This is the current best practice [31].

### Criteria for discontinuing or modifying allocated interventions {11b}

A minimum of 20 measurements in total per patient in the intervention group is necessary to be considered for inclusion in the study. Patients will be expected to measure at least twice a day (morning and evening). The intervention will always be discontinued on patient request.

### Strategies to improve adherence to interventions {11c}

The FibriCheck® app will notify participants when to measure. Participants can always do more measurements, if they so desire.

### Relevant concomitant care permitted or prohibited during the trial {11d}

Apart from the FibriCheck® measurements, medical care will continue as usual for all participants.

### Provisions for post-trial care {30}

Not applicable: This is a purely screening-based trial; there are no adverse effects to be expected solely because of screening in the intervention group. It is possible that some patients might undergo unnecessary testing. However, we expect this number to be very low due to the high negative predictive value of the app, which was estimated to be 99.7% [26]. In addition, we expect the possible benefit of earlier detection of AF to outweigh this disadvantage.

### Outcomes {12}

#### Primary outcome measures

##### Detection rate of AF in patients 65 years and older

The detection rate of AF in both the control and intervention group will be calculated after 4 weeks. A significant difference in both groups will be noted. Compared with previous studies of similar design [32–34], we will realistically assume a 2-fold increase in the detection rate of AF in the intervention group to be significant.

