## Methods: Participants, interventions, and outcomes

### Study setting {9}

This study will take place in the eligible Flemish primary care practices in the INTEGO network.

The INTEGO network is a morbidity registry containing coded contents of the electronic health records of some 400,000 patients from 100 general practitioner’s offices all over Flanders. The information is automatically collected during daily practice and contains diagnoses, year of birth, gender, prescriptions, lab results, and various biomedical parameters such as blood pressure, height, weight, etc. [1]. The INTEGO procedures have been validated by the Belgian Privacy Commission. The registry is hosted on the Healthdata platform (www.healthdata.be) [28].

Patients coming to the eligible practices, as well as the practices themselves, will be recruited separately. They will fill in separate consent forms. After consent is given by the patient, the GPs of the recruited practices will explain the study outline and specific details, such as the installation and use of the app, at the first consultation, after which the study period for that specific patient will commence. General care will proceed as normal.

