Every participant will be asked to measure at least twice a day (in the morning and in the evening) and if there are complaints such as dizziness or palpitations. After the measurement, the patient will be asked for his activities up to the measurement and certain symptoms. Participants are never asked to self-palpate their pulse, this will only take place at the GP’s office.

Measurements are available for the treating physician and a cardiologist, who will interpret the results within 24 h. Additionally, an electronic notification will be sent immediately to the interpreting physicians in case of an abnormal result. Physicians will be asked to review these results at least once every 24 h. At the end of every participant’s study period, a summarizing report will be sent to the treating physician.

When a positive result (red) has been found (indicating the possibility of AF), the patient will be contacted within 48 h for a formal 12-lead ECG. Patients themselves will also be instructed by the app to contact their GP for follow-up in case a possible AF has been found. If this ECG is inconclusive, a 2-week Holter measurement will be ordered. If AF is confirmed, rate or rhythm control and anticoagulant therapy will be started, or the patient will be referred to a cardiologist for further workup. The CHA_2_DS_2_-VASc score will be used to calculate the risk of thrombosis, and together with the HAS-BLED score [29], indicating the risk of bleeding, it will guide anticoagulant therapy [30].

If a positive FibriCheck® screening cannot be confirmed with 12-lead ECG or 2-week Holter, the patient files will be marked with a special code in the EHR and flagged for future, more intensive screening (with both the application and an ECG at consultation).

In addition to screening with the app, patients in the intervention group will also receive standard opportunistic screening: pulse palpation and a 12-lead ECG when an irregular rhythm is found.

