### Participant timeline {13}

The study will be conducted over the course of 12 months in general practices in the Flanders region of Belgium, planned to run from January 2022 to December 2022.

Allocation of control and intervention practices is planned to start around November 2021. Eligible participants will be followed in their usual primary care practice, and are recruited by the participating physician when they visit for whatever reason. They will be provided an information leaflet, a consent form, and 1 week decision time.

Participants will be followed for a total of 4 weeks. Measurements and other data will be collected and interpreted at the end of this period. After the total study period of 12 months, the resulting data will be analyzed.

A schematic overview of the timeline can be found in Table 1. A visual representation of the study flow can be found in Fig. 1.

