### Sample size {14}

The calculation hereafter is similar to that of an earlier paper, comparable to ours [34]. We used an online calculator, which can be found at http://www.sample-size.net/sample-size-proportions.

The sample size calculation was performed for the primary outcome (AF detection rate at practice level). In the INTEGO database, we found a baseline AF incidence of 13.65/1000 patients, 65 years or older, in 2015. As stated above, we estimated a realistic absolute increase of 24.57 AF cases per 1000 patients per year in the intervention group. The power calculation, with a power of 0.80 and an α of 0.05, for a two-sided two-sample *t* test, with the incidence of AF per 1000 patients per year as the outcome variable, led to a sample size of 1835 patients in each arm of the study.

As we will view the results on the practice level, the number of practices needs to be determined, considering the intra-cluster correlation coefficient (ICC). A similar study found an ICC of 0.0027 (18). As we plan to let this study run for 12 months, we wish to include 400 patients (= *m*) per practice/physician. Calculating the variance inflation factor (1 + ICC (*m* – 1)) leads us to a value of 2.077. To accommodate the expected variance, we will have to include 1835 × 2.077, or 3811 patients per arm. We will assume a loss to follow-up of 15% [32]. This brings us to a total study population of 8765 patients, or approximately 11 control and 11 intervention practices.

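### The 4-week detection rate measures short-term yield; with no later count in either arm, it cannot show that the app finds AF that usual care would otherwise miss

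*Protocol article*

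**What the plan says.** Under Outcomes {12}, the primary measure is fixed in time: "The detection rate of AF in both the control and intervention group will be calculated after 4 weeks". The effect looked for there is relative: "we will realistically assume a 2-fold increase in the detection rate of AF in the intervention group to be significant". Participant timeline {13} limits observation to the same span: "Participants will be followed for a total of 4 weeks". Section {20c} leaves patients who do not complete the 4 weeks out of the results. The 12 months in the plan are the calendar length of the study: "After the total study period of 12 months, the resulting data will be analyzed".

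Two places point to a longer window. The abstract places the comparison at the end of the study, and Sample size {14} works with a yearly rate: "we found a baseline AF incidence of 13.65/1000 patients, 65 years or older, in 2015".

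On the two strategies, Intervention description {11a} asks for at least two app measurements a day and says that pulse palpation takes place only in the GP's office. The control group receives opportunistic screening alone. App-positive patients whose AF is not confirmed are "flagged for future, more intensive screening (with both the application and an ECG at consultation").

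Section {20b} rules out additional analyses. Of the INTEGO registry, Study setting {9} says: "The information is automatically collected during daily practice and contains diagnoses".

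**The concern.** The two strategies run on different clocks. The app concentrates its search into 4 weeks, while opportunistic screening acts only when a patient attends. A count closed at 4 weeks takes in nearly everything the app period yields, but only part of what usual care will find in comparable patients over the following months.

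This matters because the background argues for more than speed. The Screening section says paroxysmal AF may escape usual methods altogether, and the aim section says the app could solve that. Testing this requires knowing what usual care goes on to find, and no planned outcome records it. The second primary outcome, average time to diagnosis, measures how soon AF is found. It does not count control diagnoses after week 4. Holter confirmations completed after week 4, and later diagnoses among flagged but unconfirmed patients, may also be lost.

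The point is separate from power: the ambiguity would remain in a trial of any size.

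**Working it through.** **Inputs.** From Sample size {14}: baseline 13.65 per 1000 per year at age 65 or older, ICC 0.0027, m = 400, two-sided alpha 0.05, power 0.80, 1835 per arm before clustering and 3811 after. From Outcomes {12}: a 2-fold effect read at 4 weeks. Assumption, not in the documents: how usual-care detections spread over the year.

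**1. The plan's own figure.** n = [1.96√(2p̄(1−p̄)) + 0.84√(p₁(1−p₁)+p₂(1−p₂))]² / (p₁−p₂)², with continuity correction. For 13.65 against 27.30 per 1000 this gives 1833, against the printed 1835 (1689 without correction). Design effect: 1 + 0.0027 × 399 = 2.077; 1835 × 2.077 = 3811. So the trial is sized for a doubling of the **annual** rate. The printed 24.57 ("we estimated a realistic absolute increase of 24.57 AF cases per 1000 patients per year in the intervention group") does not give 1835: it gives 2647 if read as the intervention rate and 735 if read as the increase. That is a separate discrepancy, and 27.30 is used below.

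**2. Share of a year's control detections after week 4.**
- Even pace: 13.65 × 28/365 = 1.05 per 1000 in the window; (13.65 − 1.05)/13.65 = 92%.
- Twice that pace around enrolment, same yearly total: 2.09 per 1000; 1 − 2 × 0.0767 = 85%.
- Three times: 3.14 per 1000; 1 − 3 × 0.0767 = 77%.

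**3. What a doubling at 4 weeks implies at 12 months.** At even pace the excess is 1.05 per 1000, equal to 4 more weeks of usual care.
- All extra cases brought forward from within the year: 13.65/13.65 = 1.00.
- All extra cases truly additional: (13.65 + 1.05)/13.65 = 1.08.
- With front-loaded control detection the upper end rises to 15.74/13.65 = 1.15 (twice) or 16.79/13.65 = 1.23 (three times).

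**4. A much larger effect is equally ambiguous at 4 weeks.** The Discussion cites a 1.4% yield from a week of screening in a similar study. As an illustration only (another population), 14 per 1000 in the app arm gives a 4-week ratio of 14/1.05 = 13. But 14 is about what usual care finds in one year. At 12 months the explanations separate: about 14 against 13.65 if diagnoses were only brought forward, and 13.65 + (14 − 1.05) = 26.60 against 13.65 if they were additional.

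**5. What a 12-month count could show.** Effective n per arm = 3811/2.077 = 1835; power by the uncorrected two-proportion formula.
- 13.65 against 14.70: difference 0.00105, standard error 0.00390. Φ[(0.00105 − 1.96 × 0.00390)/0.00390] = 0.045; the opposite tail adds 0.013; total about 6%. The 95% interval for the difference would be about ±7.65 per 1000.
- 13.65 against 27.30: Φ[(0.01365 − 1.96 × 0.00468)/0.00467] = 83%.

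**The case against.** The strongest reply is that the outcome answers the question the plan asks. Objectives {7} concern the detection rate, not AF that usual care would never find. Earlier detection is a stated benefit: section {30} on post-trial care counts it as such, and time to detection is a primary outcome. The never-found argument is background, and the abstract's remark on guidelines is hedged. This stands, and for that reason the 4-week outcome should be kept.

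A reader might infer that a positive 4-week result would be merely AF found sooner, or that the primary outcome is invalid. The documents support neither. The contrast is a valid measure of short-term yield; it only leaves open how the excess divides between earlier and additional AF.

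Three further points stand:
- The yearly rate and the abstract's wording leave some doubt about the window. If the plan were resolved towards a year of follow-up per patient, most of this point would disappear. As written, the outcome, timeline and missing-data sections all say 4 weeks.
- The 92% is not a documented figure. Patients are recruited when they visit the practice, so control detection may be front-loaded, and 13.65 is a 2015 registry incidence, not the measured yield of opportunistic screening in consented patients. Hence the range.
- Requiring a significant 12-month difference before any claim of additional AF would almost never be satisfied in the even-pace doubling case, even if every extra case were real.

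The Discussion's defence of 4 weeks concerns cumulative device yield. It justifies the length of app use, not the sole horizon for comparison with usual care.

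**Conclusion.** The point holds as a limit on interpretation and a cheap improvement, not as an error in the primary outcome. The 4-week contrast can show that the app strategy detects more AF in the short term. It cannot show that the app finds AF usual care would otherwise miss, because between about 77% and 92% of a year's control detections would fall after the window. That range assumes a yearly total of 13.65 per 1000 and a 4-week pace between one and three times the even rate; GP visit frequency is not given.

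The reading that a doubling could be entirely earlier diagnosis is possible but not established, and an excess of about 1 per 1000 is one scenario. The plan's sample size corresponds to an annual excess of 13.65 per 1000, which a 12-month count would have about 83% power to detect with 3811 analysed per arm. That figure ignores the small loss from a t test on 22 clusters. Twelve months would not exclude diagnoses brought forward by more than a year, but it says much more than 4 weeks does.

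**What to change.** 1. Keep the 4-week primary outcome and describe it as short-term yield.
2. Reconcile the 4-week window with the yearly rate in Sample size {14} and the end-of-study wording in the abstract.
3. Pre-specify one secondary outcome: cumulative confirmed AF recorded in INTEGO at 12 months from each patient's start date, in both arms, with the same denominators as the 4-week analysis. Exempt it from section {20b}.
4. Report it as a difference and a ratio with 95% confidence intervals, by the same cluster-level method. Set no significance requirement, and limit any statement about additional AF to what the interval supports.
5. State that the 12-month count includes the later repeat screening of flagged app-positive patients in the intervention arm, as part of the strategy being compared.

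**Cost.** Protocol and consent wording and one later registry extraction; no added visits or procedures. The 12-month ratio will probably be smaller than the 4-week ratio, may be imprecise, and will not be complete until a year after the last enrolment.

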##### Average time to detection of AF

We will compare the average time from the beginning of the study to the primary endpoint, the diagnosis of AF, in both study arms.

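### Average time to AF diagnosis, listed as a primary outcome, can be formed only among diagnosed patients; it is not a randomized comparison and can make the app look slower when it finds more AF

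*Protocol article*

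**What the plan says.** Outcomes {12} has a heading "Primary outcome measures" with two entries. The first is the detection rate: "The detection rate of AF in both the control and intervention group will be calculated after 4 weeks". The second is the time outcome: "We will compare the average time from the beginning of the study to the primary endpoint, the diagnosis of AF, in both study arms".

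Other sections bear on the second entry:

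- **Analysis.** Statistical methods {20a} promises an intention-to-screen analysis of all participants and names one method, a t test on cluster-level results with inverse-variance weighting. Section {20b} allows no subgroup or additional analyses. No section says what time an undiagnosed patient contributes.
- **Time frame.** Participant timeline {13} has the study "planned to run from January 2022 to December 2022", with patients recruited when they happen to visit. It also says "Participants will be followed for a total of 4 weeks". Study setting {9} describes the explanation given "at the first consultation, after which the study period for that specific patient will commence".
- **Primary status.** Objectives {7} names the detection rate alone as the primary objective. Sample size {14} uses the singular: "The sample size calculation was performed for the primary outcome (AF detection rate at practice level".

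**The concern.** A time to diagnosis exists only for someone who is diagnosed. With no rule for the others, an average of such times is an average over detected cases. Who is in that group depends on the arm, because the app is meant to add cases that usual care would miss. The two means then describe different kinds of patient, and randomizing practices does not make them comparable.

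The error can run against the intervention. Usual-care detection depends on pulse palpation at the GP's office, and patients are recruited at a visit. App detections build up over four weeks of twice-daily measurements, then need contact for an ECG within 48 hours and possibly a two-week Holter. Later app detections are therefore plausible, though the article gives no times. If they are later, each additional case found lengthens the app arm's mean, and a listed primary outcome would count the benefit as a delay.

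**Working it through.** **The plan's own figure.** None is given for time to detection. The nearest is 1835 patients per arm for the detection rate. A two-proportion calculation (two-sided α 0.05, power 0.80, continuity-corrected) gives 1833 for 13.65 versus 27.30 per 1000, the 2-fold increase in Outcomes {12}. The 24.57 per 1000 in Sample size {14}, read as the intervention rate (24.57 / 13.65 = 1.8-fold), gives 2647 and does not reproduce it. That mismatch is a separate matter; both ratios are used below.

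**Share without a time to diagnosis.** Taking the annual rates as if reached within follow-up:

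- Control: 1 − 0.01365 = 98.6%.
- Intervention, 2-fold: 1 − 0.0273 = 97.3%.
- If 24.57 is instead added to 13.65 (38.22 per 1000): 96.2%.

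Scaling the annual rates to four weeks would raise all three shares.

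**Mean among detected patients.** Let the control mean be *c*, the extra app cases' mean be *a*, and the detection ratio be *r*. If usual-care cases keep their times, the intervention mean is

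(c + (r − 1)·a) / r, which differs from *c* by ((r − 1)/r)·(a − c).

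The app arm looks slower exactly when *a* exceeds *c*, whatever the ratio above 1. All times below are assumptions; *r* = 1.8.

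| Control mean *c* | Intervention mean, *a* = 7 d | Intervention mean, *a* = 18 d | Reading |
|---|---|---|---|
| 3.9 d | (3.9 + 0.8×7)/1.8 = 5.3 d | (3.9 + 0.8×18)/1.8 = 10.2 d | slower throughout |
| 7.25 d | (7.25 + 5.6)/1.8 = 7.1 d | (7.25 + 14.4)/1.8 = 12.0 d | slower unless *a* is below 7.25 d |
| 14 d | (14 + 5.6)/1.8 = 10.9 d | (14 + 14.4)/1.8 = 15.8 d | slower only if *a* exceeds 14 d |

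**The same data with all patients included.** Assume 13.65 versus 27.30 per 1000 detected, shared cases at mean day 7 in both arms and extra app cases at mean day 14.

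- Mean among detected: control 7.0 d; intervention (7 + 14)/2 = 10.5 d. The app looks 3.5 d slower.
- Restricted mean time undiagnosed to day 28: control 28 − 0.01365×21 = 27.713 d; intervention 28 − 0.01365×21 − 0.01365×14 = 27.522 d. The app is faster, by 0.191 d per patient or about 191 days per 1000 patients.

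A simulation of 2,000,000 patients (assumed 1% persistent and 2% paroxysmal AF, no control-detectable case found later with the app) reverses in the same way. It detects 8.1 versus 21.5 per 1000. The mean among detected is 2.0 versus 7.3 d, and the restricted mean time undiagnosed is 27.79 versus 27.55 d.

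**Practice-level means.** If the annual rate is scaled to 28 days, 3811 × 0.01365 × 28/365 gives about 4 control cases, or 0.36 per practice over 11 practices. On a Poisson count, exp(−0.36) ≈ 70% of control practices would have no case and so no mean for the t test. If the annual rate were met within follow-up (3811 × 0.01365 ≈ 52 cases, 4.7 per practice), this difficulty largely disappears.

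**The case against.** **The restriction to diagnosed patients is an inference.** The article never says it, {20a} promises to include everyone, and censoring rules are often left to an analysis plan that is not shown here. It is indeed an inference. But the promise gives an undiagnosed patient no time value, and {20c} itself drops patients who do not complete the four weeks. The protocol also fixes the summary (an average), the test, the absence of other analyses and the primary status. Followed as written, no other average is available.

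**The direction is not established.** This stands. A reader might infer that the app will look slower, but the article gives no detection times and usual care continues throughout. With a control mean of 14 days the sign changes within the range shown.

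**The calendar origin.** A reader might infer that the clock starts in January 2022 for everyone, so that the outcome mostly measures recruitment date. The article does not support that as the settled reading: {9}, {11a} and {16c} all speak of a study period belonging to the individual patient. What stands is ambiguous wording.

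**Multiplicity.** A reader might infer two confirmatory tests and an inflated false-positive rate. The article does not say that time to detection alone could support a primary claim, and {7} and {14} treat the detection rate as the single primary outcome. What stands is a conflict between the heading in {12} and those two sections.

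**Conclusion.** The point holds, conditionally as to direction. Followed as written, the second primary outcome is a comparison of means within the roughly 1 to 3% of patients who are diagnosed, a subset shaped by the intervention. That does not depend on any assumed detection time or on which time origin is meant.

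Whether it would make the app look slower depends on times the article does not give. It does so when the extra app cases are found later on average than the control cases and usual-care cases keep their times. If the app also brought usual-care cases forward, the effect would shrink or reverse. In the 2-fold example the detected-only means favour control by 3.5 days, while the all-patient measure favours the app.

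The unclear origin and the two-versus-one primary outcome are lesser inconsistencies that the same edit can settle. The detection rate outcome is untouched by this point. The change should be made before the data are analyzed.

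**What to change.** 1. Keep the detection rate as the sole primary outcome, in line with {7} and {14}, and move time to detection to the secondary outcomes.
2. Start the clock at each patient's own inclusion and say so in {12}.
3. Include all patients, with undetected patients censored at the end of their 4-week window. Reconcile {20a} with the exclusion of non-completers in {20c} so that the analysed set is clear.
4. Compare cumulative incidence, or restricted mean time undiagnosed at 28 days, summarised per practice and compared at cluster level. Every practice then has a value, even with no case. Other methods that include all patients would also serve. Because most patients stay undiagnosed, differences in restricted mean time are easier to read per 1000 patients.
5. If a mean among detected cases is reported, label it descriptive.

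The cost is wording in {12} and {20a}, and in the registration if it carries the same outcome, which cannot be checked here. No new data are needed: the outcome already requires the diagnosis date, and the 4-week follow-up already requires each patient's start date.
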